#### Research Question 3 (Participants: Older Adults)

The overall experience, beliefs, and attitudes of older adults while watching the 3Scape videos will be measured using an instrument (8 items on a 5-point Likert scale and 4 open-ended questions) developed by the University of Calgary in a previous study on this technology.

#### Research Question 4

Interviews will be conducted for the therapists. Semistructured questions (topic guided) will examine the usefulness of 3Scape videos for the treatment of the mental health condition of older adults. Interviews will be audiotaped for later analysis by team members. To ensure anonymity, the older adults’ and therapists’ responses will not be connected to their identities. RA 2 will conduct the surveys. The administration of these measures will take approximately 15 minutes.

#### Research Question 5

The MBI-HSS MP will be administered to every therapist who provides the intervention to study the participants at the pretest and posttest. The administration of these measures will take approximately 20-30 minutes. RA 2 will administer these measures.

### Data Analyses

#### Research Questions 1, 2, and 3

The analyses will be conducted in SPSS using intention-to-treat principles. Descriptive statistics will be used to characterize the groups during the pretest. Owing to the small sample size, comparisons of the GAD-7, HoNOS, OPQoL-Brief, and PANAS scores within the groups will be performed using a Wilcoxon signed-rank test (*P*≤.05), and comparisons between the groups will be calculated using the Mann–Whitney *U* test (*P*≤.05). The GAD-7, HoNOS, OPQoL-Brief, and PANAS scores will be used to analyze the clinical significance, established as a change of 2 or more units [30]. Participants’ engagement will be analyzed using descriptive statistics.

#### Research Question 4

The audiotapes will be transcribed and content analysis will be performed. The content analysis will be data driven. Data codes will be inductively generated using the data collected. Through the coding, a small number of themes or categories will be generated. The analyses will be performed by an RA, and a consensus in the interpretations will be achieved through a discussion among the research team members. The validity of the interpretations will be discussed with and agreed upon by every member of the research team. NVivo 10 software will be used to conduct data analysis.

#### Research Question 5

Descriptive statistics will be used to characterize the groups at pretest and posttest. Owing to the small sample size, comparisons of the MBI-HSS MP scores within the groups will be performed using a Wilcoxon signed-rank test (*P*≤.05), and comparisons between the groups will be calculated using a Mann–Whitney *U* test (*P*≤.05).

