### Outcome Variables

#### Research Questions 1-2 (Primary Outcome Variables)

Older adults’ depressive and anxiety symptoms, mood, overall quality of life, and engagement are the primary outcome variables for these research questions. Older adults’ depressive and anxiety symptoms will be assessed using the Generalized Anxiety Disorder-7 item (GAD-7) scale patient self-report tool [21] and the Health of the Nation Outcome Scale (HoNOS; a clinician rating tool) symptoms [22], older adults’ mood will be measured using PANAS (20-item self-report questionnaire) [23], and older adults’ overall quality of life will be measured using Older People’s Quality of Life-Brief (OPQoL-Brief) questionnaire scale-13 items self-reported tool [24].

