### Sample Size

#### Research Questions 1-3 (Participants: Older Adults)

As this is a feasibility study, a sample size calculation is not required [17]. However, we can estimate the number of participants we will be able to recruit during the data collection period. In this feasibility study with a statistical power of 0.8, an α of .05, and an effect size of 1.20, the minimum required sample size will be 24 participants in total (12 in each group [19]). We aim to recruit 15 participants for each group, for a total sample size of 30, to compensate for a 20% dropout rate. Sample size calculations are estimated using G*Power (version 3.1.9.4, Universitat Kiel) [29].

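### One undirected 2-unit cut-off defines clinical significance on four unlike scales, without saying whether it applies to individuals or group means, or to which PANAS score

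*Protocol article*

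**What the plan says.** In the protocol article, Data Analyses (Research Questions 1, 2, and 3), the tests come first: Wilcoxon signed-rank within groups and Mann–Whitney between groups. The section then names GAD-7, HoNOS, OPQoL-Brief and PANAS and says their "scores will be used to analyze the clinical significance, established as a change of 2 or more units". One reference is cited for all four, and no other section qualifies the rule.

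Outcome Variables, Research Questions 1-2 (Primary Outcome Variables), describes the instruments:

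- GAD-7: "Generalized Anxiety Disorder-7 item (GAD-7) scale patient self-report tool"
- HoNOS: "Health of the Nation Outcome Scale (HoNOS; a clinician rating tool) symptoms"; no item count is given
- PANAS, for mood: "20-item self-report questionnaire"
- OPQoL-Brief, for quality of life: "questionnaire scale-13 items self-reported tool"

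The article gives no scoring range, SD, reliability coefficient or minimal important difference for any of them. It says only that the measures have good to excellent metric properties.

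**The concern.** A raw-point threshold has meaning only in relation to a particular score: its length, its scoring and its measurement error. Here one number serves an anxiety scale, a clinician symptom rating, a quality-of-life scale and an affect schedule. Four things needed to apply it are left open:

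- **Direction.** Only a change is required, not an improvement.
- **Unit of application.** The rule could classify each participant or benchmark the mean change of a group.
- **Score.** PANAS covers positive and negative affect, for which the desired directions are opposite. The rule does not say which is used.
- **Interval.** Both arms have primary outcomes at T0, T1 and T8, and the rule names no pair.

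The study is meant to supply parameters for a definitive trial, and the Discussion says it will guide therapists on the percentage of improvement to expect. A clinical-significance result that is not comparable between scales, and that can include worsening, is a poor basis for either use.

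**Working it through.** **The plan's own figure.** The 2-unit threshold has no derivation to reproduce. The sample size does reproduce: a two-sample t-test with d = 1.20, two-sided α = 0.05 and 12 per group has power 0.802, and 24/(1 − 0.20) = 30. The threshold does not enter that calculation.

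**Stringency by scale length.** The item counts are those in Outcome Variables. Points per item = 2 / number of items.

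| Scale | Items | Points per item |
|---|---|---|
| GAD-7 | 7 | 2/7 = 0.29 |
| OPQoL-Brief | 13 | 2/13 = 0.15 |
| PANAS | 20 | 2/20 = 0.10 |
| HoNOS | not stated | not calculable |

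The widest ratio is 20/7 = 2.9, which treats PANAS as one 20-item score. If it were split into two 10-item scores (an assumption), each would be 2/10 = 0.20 and the widest ratio would be 13/7 = 1.9. The scales still differ.

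**Direction.** The article states no scoring direction, so this is inferred from the constructs. Improvement is a fall on anxiety, clinician-rated symptoms and negative affect, and a rise on quality of life and positive affect. A rule requiring only a change of at least 2 is met by a 2-unit move either way on every one of them.

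**Chance of meeting the rule with no true change, applied to individuals.** Assume a normal change score with mean 0. The SD of change is not in the documents, so a range is shown. P(|change| ≥ 2) = 2[1 − Φ(2/SD)]; improvement only is half of that.

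| Assumed SD of change | Either direction | Improvement only |
|---|---|---|
| 1 | 4.6% | 2.3% |
| 1.5 | 18% | 9% |
| 2 | 32% | 16% |
| 3 | 50% | 25% |
| 4 | 62% | 31% |
| 5 | 69% | 34% |

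With whole-number scores (cut at 1.5) the either-direction figures rise to 13% at SD 1, 62% at SD 3 and 76% at SD 5. In an arm of 15, SDs of 3 to 5 give 15 × 0.50 = 7.6 to 15 × 0.69 = 10.3 participants meeting the rule by chance, half of them worse. Adding a direction therefore does not cure the problem alone: 25-34% would still appear to improve.

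**The same, applied to a group mean.** The SD of the mean change is SD/√n.

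- SD 3, n = 15: 3/√15 = 0.77, and 2[1 − Φ(2/0.77)] ≈ 1%
- SD 5, n = 12: 5/√12 = 1.44, and 2[1 − Φ(2/1.44)] ≈ 17%

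On this reading chance crossings are far rarer, about 1-17% of arms.

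**The case against.** The strongest reply is that the text speaks of clinical significance, not of response or improvement. It mentions no responder rate and no classification of individuals. A deterioration can be clinically significant, and nothing says that worsening will be pooled with benefit. The rule might only benchmark a group change. This stands in part: the 50-69% figure needs both an assumed SD and the individual reading, so it cannot be stated as what will happen. It does not rescue the rule, because the unit of application is itself undefined and the common cut-off and missing direction remain on either reading.

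The cited reference may support 2 units for one of the scales. It is not available here, so this cannot be checked. Support on one instrument would not carry over to three others of different length or direction.

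Detail of this kind is often left to an analysis plan. Here, however, the article fixes the threshold, and a later document would have to override it.

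Two stronger readings are tempting and should be resisted:

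- **A clash with the sample size.** A reader might set 2 units equal to "an effect size of 1.20" in SD units, infer an SD of 2/1.20 = 1.67 on every scale, and conclude that the study is underpowered for its own threshold. The Sample Size section ties 1.20 to no scale and no unit difference, and says a calculation is not required for a feasibility study. A threshold for meaningful change need not equal the difference a study is sized to detect.
- **Two units as a percentage of each scale's range.** The article gives no score ranges, so such percentages have no basis in it.

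**Conclusion.** The point holds as a badly fixed rule. One undirected 2-unit criterion, with the unit of application and the PANAS score undefined, cannot mean the same on four unlike scales, and read literally it admits deterioration. The difference in length is documented for three of the four scales. The opposite directions are inferred from the constructs.

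The effect of noise is conditional. It is large (50-69% in either direction, 25-34% apparent improvement) if individuals are classified and the SD of change is 3 to 5 points. It largely disappears at an SD of about 1 or less, and it is much smaller for group means.

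A reader might infer that the trial's hypothesis tests are compromised, but the Wilcoxon and Mann–Whitney comparisons do not use the threshold. Nor does the article say that the threshold will set the definitive trial's target difference. What is affected is the clinical-significance result alone. It should be corrected before analysis, but it does not threaten the rest of the plan.

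**What to change.** In Data Analyses, replace the common rule with the following:

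1. A separate criterion for each of GAD-7, HoNOS, OPQoL-Brief, PANAS-positive and PANAS-negative, stating the score used and the direction that counts as improvement.
2. A cited source for each threshold. Where none applies, use a reliable-change index: 1.96 × SD × √[2(1 − r)], with SD the T1 standard deviation and r a sourced reliability. With no true change this classifies about 2.5% in each direction. Half an SD should not be used alone: it is exactly 2 units at a T1 SD of 4 and only 1.5 units at an SD of 3, so it need not be stricter than the present rule.
3. Application to individual change from T1 to T8, which both arms complete for GAD-7, HoNOS and OPQoL-Brief.
4. Improvement and worsening reported separately by arm, with a risk difference and 95% CI. With 15 per arm the interval will be wide and should be read descriptively.

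For PANAS, reconcile the schedule first. Table 1 marks it for both arms at T0, T1 and T8. Data Collection Methods (Research Questions 1-2) describes it only after video sessions in the intervention group and leaves it out of the measures given to both arms. A comparison between arms is possible only if controls are measured.

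The cost is a few more lines of analysis text. GAD-7, HoNOS and OPQoL-Brief need no new data, and neither does PANAS if Table 1 is followed. Improvement rates may come out lower than under the present rule.

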### Ethics and Dissemination

#### Research Ethics Approval

All procedures were approved by the ethics committee of Alberta University and the Northern Alberta Clinical Trials Research Centre, Canada.

#### Incentives

The participants will not receive any incentive for participating in this study.

#### Withdrawal From the Study

The participants and substitute decision makers can request to withdraw from the study at any time either orally or in writing. The participants will be able to withdraw from the study at any time before the group analysis is calculated. If a participant withdraws, his or her information will not be taken into account in the analysis. In the event that a participant requests to have his or her data destroyed, the research team will honor this request by shredding and recycling the paper records and erasing any records stored on a computer hard drive using commercial software applications designed to remove all data from storage devices. However, once all of the participants’ data have been analyzed, the participant cannot withdraw. The participants will be informed of this in a consent letter. The deadline for withdrawal will be once all of the participants’ data have been collected and data analysis is underway. This will occur during the 8 months of the study.

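### The withdrawal rule drops all information on anyone who withdraws, which contradicts the intention-to-treat statement and may bias the comparison between arms

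*Protocol article*

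**What the plan says.** The Data Analyses section, for research questions 1 to 3, states: "The analyses will be conducted in SPSS using intention-to-treat principles". For the clinical scales it adds that "comparisons between the groups will be calculated using the Mann–Whitney" test, with signed-rank tests within groups.

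The Withdrawal From the Study section states: "If a participant withdraws, his or her information will not be taken into account in the analysis". The window is wide: "The participants will be able to withdraw from the study at any time before the group analysis is calculated". Physical destruction is a separate provision that depends on a request: "In the event that a participant requests to have his or her data destroyed, the research team will honor this request".

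The Sample Size section sets the target at 15 per group, 30 in total, "to compensate for a 20% dropout rate". The Blinding section says that participants and therapists know the allocation and that only the outcome assessors are blinded.

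**The concern.** Intention to treat means that a randomised participant is analysed in the arm to which he or she was allocated, using the outcome data that exist. The withdrawal sentence takes a randomised participant out altogether because of something that happened after randomisation. It does so even if the week 18 outcome has already been recorded and the participant has no objection to its use. Whoever carries out the analysis must break one of the two statements, and the article does not say which one gives way.

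The stake is the randomised comparison. Participants know their arm, and the arms differ in what is offered: in the experimental arm, five video sessions replace one therapy group. Leaving could therefore depend on arm and on how the person is doing. If it does, excluding the leavers distorts the between-group estimate. The Discussion intends these estimates to feed sample size calculations for future trials, so a distortion would carry forward.

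**Working it through.** **1. The two rules applied to the same participant**

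| Randomised participant who… | Under the Data Analyses section | Under the withdrawal section |
|---|---|---|
| withdraws after week 18 is measured, no request for removal | analysed in the allocated arm | excluded |
| withdraws between weeks 12 and 18, no request for removal | week 0 and week 12 data kept | excluded |
| withdraws and asks for destruction | data not available | data destroyed |
| misses sessions or an assessment without withdrawing | analysed in the allocated arm | not addressed |

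The rules conflict in the first two rows only. The third row shows that the general exclusion is not needed to honour destruction requests.

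**2. The plan's own figures**

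The inputs are "with a statistical power of 0.8, an α of .05, and an effect size of 1.20". An exact two-sided two-sample t-test needs 12 per arm (power 0.802), as the plan states. Inflating for dropout gives 12 / (1 − 0.20) = 15 per arm, also as stated. Expected dropout is 30 × 0.20 = 6, or 15 × 0.20 = 3 per arm if even. This is an upper limit for the withdrawal rule, because planned dropout is not the same as formal withdrawal.

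**3. Simple illustration (assumed mechanism)**

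Suppose 12 participants in one arm have mean *m*, and 3 who withdraw would have ended 1 SD worse.

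- Mean of all 15: (12*m* + 3(*m* − 1)) / 15 = *m* − 3/15 = *m* − 0.20.
- Mean after exclusion: *m*.
- Shift: 0.20 SD, and 0.20 / 1.20 = 17% of the planned effect.
- If the three end only 0.5 SD worse: 3/15 × 0.5 = 0.10 SD.
- If the same pattern occurs in both arms: 0.20 − 0.20 = 0.

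**4. Simulation check (assumed mechanisms)**

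Normal outcomes with SD 1, 15 per arm, true effect zero, Mann–Whitney test at .05, 20,000 runs. Each cell gives bias in SD, then the rejection rate.

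| Excluded (one arm v other) | Unrelated to outcome | Correlation 0.5 with outcome | Worst outcomes leave |
|---|---|---|---|
| 3 v 3 | about 0; 0.047 | about 0; 0.050 | about 0; 0.088 |
| 3 v 0 | about 0; 0.045 | 0.16; 0.067 | 0.33; 0.140 |
| 6 v 0 | about 0; 0.051 | 0.31; 0.108 | 0.61; 0.340 |

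With nobody excluded, bias is about 0 and the rejection rate is about 0.044. The last row puts all six planned dropouts in one arm and is an extreme case. The documents give no withdrawal rate by arm, so none of these rows is a forecast.

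**5. Power**

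At an effect of 1.20, t-test power is 0.887 with all 30 analysed, 0.802 at 12 v 12, and 0.776 at 15 v 9. The plan already allows for the 12 v 12 case, so power is not the main issue.

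**The case against.** Several points on the other side stand.

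- **Exclusion is not destruction.** A reader might infer that every withdrawn participant's data are deleted. The article does not say so: withdrawn participants are left out of the analysis, and records are destroyed only on request.
- **Bias is not certain.** It needs withdrawal that is related to outcome and differs between arms. The illustration and the simulation both give about zero otherwise.
- **This is not shown to be a completers-only analysis.** The rule covers people who ask to withdraw. Those who miss videos or an assessment without withdrawing still fall under the intention-to-treat statement.
- **Retention is not shown to be hidden.** A reader might infer that the retention estimate is biased. No such estimate is defined, and leaving out outcome data does not prevent a count. The coordinator allocates and codes each participant, the trial commits to CONSORT for feasibility studies, and a participant flow figure is included.
- **Changing the sentence recovers only part of the data.** Under the planned rank tests, someone with no week 18 value cannot enter a week 18 comparison. For that comparison the gain is mainly people who withdraw after week 18 is measured. Earlier data remain useful for describing the groups, for the week 0 to week 12 comparisons, and for whatever missing-data method the SAP may specify.

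It can also be said that this is a 30-person study whose stated primary objective is feasibility, so the comparisons are exploratory. That lowers the consequence but does not remove the conflict. Nor can the conflict be left to an unseen SAP, because both statements are explicit in the article.

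**Conclusion.** The point holds as a contradiction with a conditional risk of bias. The withdrawal section excludes all information on every participant who withdraws, including outcomes already measured and without any request for removal. That is not intention to treat, and the two sections must be reconciled.

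The effect on the comparison may be nil. It is of the order of 0.20 SD if 3 of 15 in one arm only are excluded and would have ended 1 SD worse. Under the simulated mechanisms with 3 leaving one arm for outcome-related reasons, it is 0.16 to 0.33 SD. These sizes rest on assumed mechanisms and on treating planned dropout as formal withdrawal, which makes 6 of 30 an upper limit. The documents do not support saying that all withdrawn data are destroyed, that the effect estimate is necessarily biased, or that retention cannot be estimated.

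**What to change.** - In the Withdrawal From the Study section and the consent letter, replace the exclusion sentence. Data collected up to withdrawal are kept and analysed in the randomised arm, unless the participant or substitute decision maker asks for removal or destruction.
- In the Data Analyses section, state that the analysis set is all randomised participants with data, apart from such removals.
- Report withdrawals and removals by arm.

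The choice of method for missing week 18 values can be left to the SAP.

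The cost is one sentence in the protocol and consent letter, one line on the analysis set, and an ethics amendment. The new terms would apply to participants who consent to them, so the change is best made before further consent is taken. The article reports the study on hold as of August 2021, which would be a convenient time.

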#### Consent or Assent

Signed consent will be obtained from all participants in the study. For those who are unable to provide their informed consent, one of the therapist researcher ([name]), or another therapist involved in the recruitment process, will approach each potential participant and his or her substitute decision maker to provide information on the study. If these potential participants and their substitute decision makers provide their consent, the substitute decision makers will sign the consent form, and we will seek the potential participants’ assent.

#### Confidentiality

We will assign numerical codes to the participants instead of using their names or other identifiers. Only the study coordinator will have access to the master list, where these codes are linked to the participants’ first names. With the exception of direct conversations with each participant, their names will not be used, only their numbers. Hard copies of the consent forms, questionnaires, and study notes will be stored in a locked filing cabinet in a laboratory ([name], Faculty of Rehabilitation Medicine, University of Alberta). All of the de-identified electronic study documents will be encrypted and stored on a password-protected computer located in a laboratory ([name], Faculty of Rehabilitation Medicine, University of Alberta).

#### Access to Data

All PIs will be given access to the cleaned data sets. The master list will be stored on a password-protected computer, located in the PI’s laboratory ([name], Faculty of Rehabilitation Medicine, University of Alberta). Only the study coordinator will have access to the master list. The data will be retained for 5 years. There are no plans for future use of data other than publishing them in peer-reviewed journals and at conferences. The data will not become part of a data repository and will not be involved in the creation of a research database or registry for future research use. After 5 years, the data will be destroyed. This will be done by shredding the paper records. Records stored on a computer hard drive will be erased using commercial software applications designed to remove all data from storage devices.

